##### Service utilisation

As a way to track participants service utilisation, participants will be asked to complete a questionnaire, developed by the researchers, about the services that they are accessing. The following questions are included in the questionnaire: Do you or your child currently attend any health services? (question 1); if participants indicate ‘Yes’ on question 1, they will also be asked: Do you and/or your child currently attend any of the following services? (Psychologist, Social worker, Paediatrician, Occupational therapist, Speech pathologist, Early childhood education/intervention centres, Other) (question 2); who is receiving this service (you, your child, both)? (question 3); when did you/your child begin attending the service/s? (question 4); and how frequently do you/your child attend the service (e.g., weekly, monthly)? (question 5).

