Families with lower level risks will be connected with local services and might also be provided with information on online resources (e.g., free to access online parenting programs such as ParentWorks [19] or Movember Family Man [20]) or therapist-assisted interventions (e.g., online or in-person Parent-Child Interaction Therapy [21]). For families who are at high risk, in addition to receiving resources and linkages to services as mentioned above, they will receive in-person assessments (through a KIDS-Connect hub [22] with capacity to reach families at homes or other community facilities) to determine the complexity of health needs followed by appropriate referrals and a ‘warm hand-over’ (i.e., directly linking patients to services in a supportive manner) to recommended services. The duration of in-person (or digital as indicated in extreme circumstances) assessments will depend on the needs identified by the WMG-E, however, these assessments generally range from 30 to 60 min [22]. Once the in-person assessment is completed and families are linked with recommended services, the type and duration of services they receive will depend on their needs. For example, families with psychological needs may receive ten 60-min sessions with a psychologist while families with unmet psychosocial needs who access services such as Uniting (community service agency) [22, 23] may receive 2–3 sessions targeted at addressing psychosocial needs. Furthermore, these families will receive follow-up support by the navigator to ensure engagement with recommended services and continuity of care. Follow-ups will occur fortnightly via telephone for a duration of 10 to 20 min.

We hypothesise that in the first 6 months, the intervention group will have better access and engagement with services due to this group not only getting linked up with services but also continuity of care through the service navigator to ensure the uptake of recommended services. Further we hypothesize that, families in the intervention group that are connected with services will also show a significantly greater increase in wellbeing relative to the control group, at the 12 month follow up. This is because, via the service navigator, they will have assistance in connecting with services and ongoing monitoring and support to ensure that their needs are being met.

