#### Analysis

##### Sample size calculations

A sample of 244 families will provide greater than 99% power in finding an increase from the current service utilisation of 30% doubling it to 60% in the intervention group with statistical significance at 5%. Taking non- and partial-adherence and sample dropout into account at 5%, the required sample size was revised to 300 (150 per group)*.*

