### Limitations

Due to the nature of the intervention, it is not possible for participants or service navigators to be blinded to study conditions. Furthermore, the services that participants are connected with will vary depending on their needs. It will therefore be difficult to determine whether improved outcomes are due solely to the service navigator, the service attended, or a combination of both.

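### The service-use questions do not separate contacts the trial delivers to the intervention arm from outside services, so delivery of the intervention could be recorded as uptake

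*Protocol article*

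**What the plan says.** The Service utilisation part of the Measures section describes the outcome as self-report: "participants will be asked to complete a questionnaire, developed by the researchers, about the services that they are accessing". Question 1 is "Do you or your child currently attend any health services". A 'Yes' opens question 2, whose options are "Psychologist, Social worker, Paediatrician, Occupational therapist, Speech pathologist, Early childhood education/intervention centres, Other". Questions 3 to 5 ask who receives the service, when it began and how often it is attended. None of the five mentions the navigator, the study team or KIDS-Connect.

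The Sample size calculations section powers the trial on this outcome, for "an increase from the current service utilisation of 30% doubling it to 60% in the intervention group". The Statistical analysis section models service utilisation with a logit link at three time points and states no exclusion.

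The intervention itself involves contact with families. The Background says the navigator keeps contacting the family every two weeks and gives no end date. The Randomised controlled trial section adds: "Follow-ups will occur fortnightly via telephone for a duration of 10 to 20 min". For high-risk families the same section says "they will receive in-person assessments (through a KIDS-Connect hub [22] with capacity to reach families at homes or other community facilities", and that "these assessments generally range from 30 to 60 min". The Care-as-usual group section states that controls have no navigator. The Limitations section concedes that "it is not possible for participants or service navigators to be blinded to study conditions".

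**The concern.** The Objectives concern access to services and uptake of service recommendations. The navigator is the means to that end. If a family's contact with the navigator can itself be entered as a service, part of the intervention's delivery may be counted in the outcome it is meant to change.

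The contact occurs in one arm, so the error would be differential. A control family has no navigator call to report. The respondent also knows the allocation. A positive result on the only powered outcome could then be challenged on the ground that some of the difference is the trial reporting its own activity. With the form as printed, the data to answer that challenge would not be collected: an entry of 'Other' with a start date and a frequency does not identify the navigator.

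**Working it through.** **1. The plan's own figure.** Inputs from Sample size calculations: 244 families, so n = 122 per arm; p0 = 0.30; p1 = 0.60; significance 5%, taken as two-sided because the article does not say.

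Power = Φ[(p1 − p0 − 1.96 × √(2p̄(1 − p̄)/n)) / √((p0(1 − p0) + p1(1 − p1))/n)], where p̄ is the mean of p0 and p1.

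With p̄ = 0.45, the two standard errors are 0.0637 and 0.0607. (0.30 − 0.1248)/0.0607 = 2.88, and Φ(2.88) = 99.8%. The stated power above 99% is reproduced and is not in dispute.

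**2. Which trial contacts could meet the wording.**

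| Contact | Who receives it from the trial | Fit with question 1 or 2 |
|---|---|---|
| Navigator, fortnightly, 10 to 20 min by telephone, no stated end | Intervention arm only | May still be running at Time 2; could be entered as 'Other' or 'Social worker'; a call is not naturally something one attends |
| KIDS-Connect assessment, 30 to 60 min, in person | High-risk intervention families only | Something one attends, but rarely still current at 6 or 12 months |
| Outside service reached through navigator or hub | Mainly intervention arm, by design | A genuine intended effect; must count |

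The Economic analysis section costs the care coordinator separately from completed service referrals. The outcome section makes no such separation.

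**3. How sensitive the outcome is.** The documents give no rate of such answers. Let c be the assumed share of intervention families using no outside service who answer 'Yes' only because of trial contact. Assume no true effect, so that 30% in each arm use an outside service. The apparent intervention rate is then 0.30 + 0.70c. Putting this rate in the formula as p1, with n = 122, gives the chance of a significant result in favour of the intervention. This is a simple two-proportion comparison, not the planned multilevel model.

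| Assumed c | Apparent rate | Points added | Share of planned 30 points | Chance of significance |
|---|---|---|---|---|
| 0 | 30.0% | 0 | 0% | 2.5% |
| 5% | 33.5% | 3.5 | 12% | 8.5% |
| 10% | 37.0% | 7.0 | 23% | 21% |
| 20% | 44.0% | 14.0 | 47% | 62% |

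Producing the whole planned difference would need c = 0.30/0.70, about 43%. The table shows only what follows if c is not zero. It does not estimate c.

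**The case against.** A reader might infer that delivering the intervention by itself produces part of the effect, so that the arms would differ even if no intervention family reached an outside service. The documents do not support that.

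- The item asks what the family currently attends. Routine navigator contact is a short telephone call, largely to check on engagement with other services. Nothing calls the navigator a social worker or a clinician, and many families would not list the calls. This stands, and it is why zero belongs in the range. It does not dispose of the point: the article introduces the form as covering services families are accessing, and the form is used in translation or through interpreters, so a single verb is a weak safeguard.
- Outcomes are asked at 6 and 12 months, which the Assessments section labels post-intervention. A single assessment would rarely be current by then. This stands for the hub. It does not settle the navigator, whose contact has no stated end; the service hypothesis is about the first 6 months.
- It is also tempting to say that no control family could count the hub, or that hub contact continues after the assessment. Controls with identified risk are told to seek local services and are not barred from KIDS-Connect. The article describes an assessment followed by referral and hand-over, not continuing care there.
- Both arms are guided towards services for more detailed assessment, so a hub assessment is arguably access rather than delivery. Coding it as no service could bias against the intervention. This stands and shapes the fix.
- Respondent instructions and coding rules are often left to fuller documents. That is true, but here the article prints the questions, and those questions do not collect what later coding would need.

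**Conclusion.** The point holds as a weakness in the stated wording of the only powered outcome. The five questions cannot distinguish a family whose only contact is the navigator from one attending an outside service, and navigator contact is confined to one arm. The KIDS-Connect assessment carries the same problem, less plausibly.

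The direction is clear: any such misclassification would favour the intervention. The size is not. The documents do not show how families would answer, how many are high risk, or whether calls continue at Time 2. Under the assumptions shown, values of c from 0 to 20% add 0 to 14 points. No value in that range can be preferred from the documents, and zero is possible. The change is worth making because it is nearly free and protects the main result, not because bias has been shown.

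**What to change.** - Add one sentence to question 1, the same in both arms and at every time point: 'Do not count calls or messages from the study team or service navigator.'
- Add a service-name field to question 2. Have someone unaware of arm code entries naming only the navigator as 'No', by a rule written in advance, since such an entry hints at the arm.
- Record the trial-arranged KIDS-Connect assessment as its own category, report it separately, and show the service-use result with and without it.
- State that outside services reached through the navigator or the hub still count.

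The cost is one sentence, one text field and one category in a researcher-developed REDCap form, carried into each language version, plus a short coding rule. Randomisation follows the Time 1 questionnaires, so no family has had navigator contact by then and the instruction should not alter baseline answers. The small downside is that observed service use in the intervention arm may be slightly lower.

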## Objectives

The primary objectives of the Randomised Controlled Trial (RCT) component involving families of children aged 6 months to 3 years from CALD, regional and rural communities in NSW are to evaluate: (1) the engagement with developmental surveillance; (2) access to services for those with mental health and social care needs; and (3) uptake of service recommendations. Secondary objectives will include examining (1) the effectiveness of the WMG-E platform in identifying and addressing parental mental health, parental psychosocial and child developmental needs; and (2) whether a service navigator, in addition to the WMG-E platform, increases family wellbeing by facilitating access to relevant services and by providing continuity of care.

The objective of the implementation evaluation is to ascertain the acceptability, feasibility and the impact of the WMG-E platform and service navigator.

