#### Procedure

##### Recruitment

Families attending child and family health services, refugee health services, supported playgroups, parenting groups, NGO services, GP clinics, special paediatric clinics, or Child and Family Health Nurse services in Murrumbidgee LHD and Fairfield LGA will be informed about the study by their service provider. They will also be provided with a quick response (QR) code with a hyperlink to the WMG-E app which they can access using tablet devices provided by the service they are attending or using a personal smartphone. Families will be excluded from the research if they are allocated to the control group but are in “acute crisis” based on their questionnaire responses (i.e., K10 > 25 and/or risk of homelessness, domestic violence, loss of electricity, or no food). These families will automatically be considered RCT dropouts and will be contacted by a researcher who will assist them in engaging with services.

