##### Assessments

All participants will complete consent forms and a demographic information questionnaire along with the study questionnaires through the REDCap platform. These questionnaires will be made available in English, Vietnamese, Arabic, and simplified Chinese (the four most common languages spoken in NSW). Where translated versions of questionnaires exist, they will be used, otherwise a licensed interpreter will be commissioned to translate the questionnaires during assessment. Those who cannot speak English will be linked up with services with access to interpreters as part of their service delivery. The demographic questionnaire, which will be completed at trial entry (baseline), will include the child’s date of birth, the child’s gender, whether the child was born premature, the child’s country of birth, the mother’s age, the mothers education level, the mother’s country of birth, the fathers age, fathers education level, the father’s country of birth, parent marital status, socioeconomic status, and the main language spoken in the home. The study questionnaires will be completed at three time points: baseline [Time 1], six-months post-intervention [Time 2], and 12-months post-intervention [Time 3]. See Figs. 1 and 2 for a summary of participant flow through the study.

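### The service-utilisation questionnaire records only current attendance at health services, so finished courses and social-care-only use can be scored as no use, which is likely to dilute the 30% versus 60% contrast

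*Protocol article*

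**What the plan says.** In the Protocol article, Measures, Service utilisation, question 1 reads "Do you or your child currently attend any health services". The article continues "if participants indicate ‘Yes’ on question 1, they will also be asked" and lists four further questions: which services (also in the present tense, with social worker and an open category among the options), who receives them, when attendance began, and how often. No listed question asks for an end date or about a service already finished.

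The Randomised controlled trial section gives examples of the care that linkage may lead to: "families with psychological needs may receive ten 60-min sessions with a psychologist", or two to three sessions with a community service agency. Assessments are at baseline, 6 months and 12 months. The Objectives include "access to services for those with mental health and social care needs" and the uptake of recommendations. Recruitment begins with "Families attending child and family health services, refugee health services, supported playgroups" and goes on to GP, paediatric and nurse services, as well as parenting groups and NGOs.

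Sample size calculations assumes present utilisation of 30% rising to 60%, with 244 families and more than 99% power. Statistical analysis models service utilisation with a logit link and does not name the question that defines a yes.

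**The concern.** The questionnaire describes a family's status on the day it is completed, while the objectives concern whether the family got to a service at all. Three gaps follow.

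- **Finished courses.** A family that is linked, attends and finishes before Time 2 or Time 3 has nothing current to report. Faster linkage makes this more likely, so the loss may fall most on the navigator's own effect.
- **Social care.** WE CARE screens for housing, food, utilities, employment, education and childcare. A family helped only with these can answer no to a question about health services and never reach the option list.
- **Existing attendance.** A family recruited at a health service may answer yes at every time point in either arm, whatever was recommended to it.

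The first two gaps can hide uptake. The third, if question 1 is the endpoint, adds the same background to both arms. At stake is the only outcome with a sample-size calculation. An analysis plan can choose among the answers collected, but it cannot recover answers to questions that were not asked.

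**Working it through.** **Inputs from the article.** 30% versus 60%; 5% significance (taken as two-sided, since sidedness is not stated); 244 families allocated 1:1, so n = 122 per arm.

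**Formula.** Pooled-variance normal approximation for two proportions, with d = p2 − p1 and p̄ = (p1 + p2)/2:

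- se0 = √[2p̄(1 − p̄)/n]
- se1 = √{[p1(1 − p1) + p2(1 − p2)]/n}
- power = Φ[(d − 1.96·se0)/se1]

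**The plan's own figure.** p̄ = 0.45, se0 = 0.0637, se1 = 0.0607. (0.30 − 1.96 × 0.0637)/0.0607 = 2.88, so power is 99.8%. The stated figure of more than 99% reproduces. The arithmetic is sound; the question is whether the questionnaire measures the quantities it assumes.

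**Sensitivity.** The article gives no rate for either distortion, so the shares below are assumptions shown as a range.

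(a) A share m of the intervention's added uptake is missed because it has finished or is social care only: p1 = 0.30, p2 = 0.30 + 0.30(1 − m).

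(b) A share f of families in both arms answers yes because of a health service already attended: p1 = f + 0.30(1 − f), p2 = f + 0.60(1 − f). The difference shrinks to 0.30(1 − f).

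(c) A share m of all use is missed equally in both arms: p1 = 0.30(1 − m), p2 = 0.60(1 − m).

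| Case | Control | Intervention | Power, n = 122 |
|---|---|---|---|
| Plan | 30% | 60% | 99.8% |
| (a) m = 0.25 | 30% | 52.5% | 95% |
| (a) m = 0.50 | 30% | 45% | 68% |
| (a) m = 0.75 | 30% | 37.5% | 24% |
| (b) f = 0.20 | 44% | 68% | 97% |
| (b) f = 0.50 | 65% | 80% | 75% |
| (b) f = 0.80 | 86% | 92% | 32% |
| (c) m = 0.25 | 22.5% | 45% | 96% |
| (c) m = 0.50 | 15% | 30% | 80% |
| f = 0.20 with (a) m = 0.25 | 44% | 62% | 81% |
| f = 0.50 with (a) m = 0.50 | 65% | 72.5% | 24% |

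Worked row, (a) m = 0.50: p̄ = 0.375, se0 = 0.0620, se1 = 0.0612; (0.15 − 0.1215)/0.0612 = 0.47, so power is 68%.

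**Planned recruitment.** 300 less the stated 5% is 285, or 142 per arm. With 142 per arm, 30% versus 45% has power of about 75% instead of 68%. The larger sample softens the loss but does not remove it.

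**The case against.** Several replies have force.

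- The 30% is itself described as current utilisation, so it may be a point prevalence that matches the question's tense. A reader might treat it as ever-use and conclude that both arms would collapse to very low observed rates. The article does not support that: its session counts are examples, duration is said to depend on need, and the listed services include some that may run for a long time.
- The article does not say that question 1 is the endpoint. For families past the gate, service type and start date can separate new services from existing ones, and social worker and the open category capture some social care. This stands, and it makes the recruiting-service problem conditional on how the outcome is derived. It does not help with finished courses or with families stopped at the gate.
- Not all recruitment settings are health services, and whether a parent at a GP visit would report current attendance is unknown.
- The Economic analysis costs completed referrals in both arms, so some record of them may be intended. The article does not say how it is obtained or that it feeds the utilisation outcome.
- A reader might want the outcome restricted to families with a flagged need. Recruitment excludes control families in acute crisis after allocation but has no such exclusion for the intervention arm, so the restriction would concentrate that imbalance.

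Who is analysed and how Time 2 and Time 3 are dated are separate questions, not defects of this questionnaire.

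**Conclusion.** The questionnaire as described can record genuine users as non-users in two identifiable groups: families whose course has finished and families who used only social care. If question 1 defines the outcome, it can also count attendance that predates the trial. The likely result is dilution of the planned contrast and an imperfect match with the second and third primary objectives.

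The size is unknown. Small distortion (a quarter of added uptake missed, or a fifth of families already answering yes) leaves power at 95% or more. Half missed gives 68%, and half already answering yes gives 75%. Only larger or combined distortions bring it to about a quarter. A reader might infer that the trial cannot show a change from 30% to 60%; the figures do not support this, because they rest on shares that the documents do not give. The change should be made because it is cheap and the missing answers become harder to recover as families pass Time 2.

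**What to change.** 1. At Time 2 and Time 3, ask which services the parent or child has attended at any time since the previous questionnaire. Keep current attendance at Time 1 as the baseline.
2. Remove the health-services gate so that every family sees the service list.
3. Add social-care options that match the WE CARE needs (for example housing, food or financial relief, utilities, employment, education, childcare, community support), and an end date beside the start date.
4. Define the binary outcome as at least one service begun after randomisation, taken from the start date and excluding the recruiting service, in all randomised families.
5. State the 30% and 60% on that definition and recheck the power. Because a service begun after randomisation cannot exist at Time 1, the model would take Times 2 and 3 as outcomes, with Time 1 attendance as a covariate.

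The cost is editing a questionnaire that the researchers wrote themselves, re-translating a few items, and some wording in the analysis plan. Recall over 6 months is less exact than current status, and families already past Time 2 would need a retrospective question.
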